#### Moderating variables

Several variables may be associated with intervention outcomes and will be examined as moderators in statistical analyses (race, sexual orientation, sex, and baseline service connection). The relationship between sex and increased risk for suicide attempts has been found to be consistent among YEH with female youth attempting suicide more often than males [8, 10]. However, females complete suicide less often than males [31]. Youth who identify as Black and/or as a sexual minority are overrepresented in the YEH population. Compared to YEH who identify as White, Black YEH have decreased risk of suicidal thoughts [32] and attempts [33]. However, sexual minority youth are more than twice as likely to attempt suicide than their heterosexual counterparts [7]. Finally, some research suggests that service-connected youth have different needs than service disconnected youth. Service disconnected youth report more severe mental health problems, substance use, and other risks [34]. Therefore, youth not accessing services are likely the most in need of assistance, and the least likely to receive it, which is of concern since service connection is a consistent predictor of improved mental health, biological, and social functioning overall [26]. An examination of individual variation through the moderation analyses will allow further specification within subgroups of treatment response.

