### Sample size {14}

The power analyses were conducted using the Monte Carlo simulation method [59]. For the LGMs proposed under Aim 1, previous intervention work established a medium to large effect size for treatment differences on suicidal ideation, with *r*s ranging from 0.42 to 0.77 [60] and Cohen’s *d* ranging from 0.64 to 1.03 [61] from 3- to 12-month post-baseline, favoring the cognitive behavioral treatment. Similarly, treatment differences on secondary outcome, depressive symptoms, also have shown medium to large effect sizes, with *d* ranging from 0.39 to 1.24 for depressive symptoms across 6 months [62]. Aim 1 analyses will compare the growth curves of CTSP + SAU to SAU alone. The proposed sample size is 300, assuming an attrition of 10, 15, 15, and 20% at the 3-, 6-, 9-, and 12-month follow-up (Table 2). For the LGMs, under the conditions of continuous outcome variables (e.g., suicidal ideation) and a dichotomous covariate (i.e., two intervention conditions) that has a regression coefficient of 0.20 (medium effect size) for the slope growth factor [59], a sample size of 300 can produce a power of 0.98 to detect the treatment effect on the growth rate of the outcomes. For Aim 2, mediation analyses (path models) are proposed to identify the mechanisms that underlie the treatment effects. Previous clinical trials have reported treatment differences of medium to large (*d* = 0.49 to 0.88) effect sizes for the proposed mediators, such as perceived burdensomeness [61]. Following the three-path mediation model specification suggested by Thoemmes et al. [63], and assuming medium effect sizes for the path coefficients, the proposed sample size can provide sufficient power (0.92) to detect mediation effects.

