## Assignment of interventions: allocation

### Sequence generation {16a}

At the end of the baseline assessment, we will use an urn randomization computerized program to ensure that the two study conditions are balanced by baseline service connection and other moderating variables (sex at birth, race, identify as sexual minority).

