## Statistical methods

### Statistical methods for primary and secondary outcomes {20a}

Latent growth models (LGM) and mediational models, as described below, will be estimated using MPlus 8 program and evaluated using generally accepted criteria including chi-square, RMSEA, CFI, and SRMR model fit statistics.

#### Study aim 1

The impact of the two study conditions (i.e., CTSP + SAU and SAU alone) on the outcomes will be tested in Aim 1. For suicidal ideation, a latent growth model (LGM) will be applied to the longitudinal data across 5 time points (baseline, 3, 6, 9, 12 months) to estimate the trajectories of change in suicidal ideation over time. Treatment effects on estimated growth parameters, including the intercept (the initial status) and the slope (trends of change over time), will be specifically tested. It is expected that those assigned to CTSP + SAU will show a sharper decrease in suicidal ideation and maintain a lower level following the treatment than those assigned to SAU alone. Similar LGM and follow-up analyses will be conducted on the secondary outcomes, substance use frequency, and depressive symptoms.

#### Study aim 2

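### The Aim 1 growth model as described leaves out the four factors used to balance allocation; naming them as covariates would avoid a mildly conservative standard error at almost no cost

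*Protocol article*

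**What the plan says.** Sequence generation {16a} describes a computerised urn that keeps the two conditions "balanced by baseline service connection and other moderating variables (sex at birth, race, identify as sexual minority").

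Statistical methods {20a}, Study aim 1, says that for suicidal ideation "a latent growth model (LGM) will be applied to the longitudinal data across 5 time points (baseline, 3, 6, 9, 12 months"). It continues: "Treatment effects on estimated growth parameters, including the intercept (the initial status) and the slope (trends of change over time), will be specifically tested". No covariate is named there. The same model is to be used for substance use frequency and depressive symptoms.

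Sample size {14} powers this model with "a dichotomous covariate (i.e., two intervention conditions") and a "regression coefficient of 0.20 (medium effect size) for the slope growth factor". It concludes that "a sample size of 300 can produce a power of 0.98 to detect the treatment effect on the growth rate of the outcomes".

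Two other places bear on which covariates enter. Under {20b}, Outreach worker effects, outreach worker becomes a control variable in the growth and mediation models only if a preliminary analysis of variance is significant. Under {20b}, Study aim 3, the four balancing factors are added to the Aim 1 analysis of the primary outcome one at a time, each with its interaction and direct effect, to explore moderation.

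**The concern.** Allocation and analysis do not match. When allocation pushes the arms towards balance on a factor that predicts the outcome, chance imbalance in that factor contributes less to the sampling error of the treatment effect. A model that omits the factor still counts its variance as residual. Its standard error is then larger than the real sampling error, the confidence interval is too wide and the test rejects too rarely under the null.

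The protocol itself gives some reason to think that the factors matter. The Moderating variables section of the Introduction links them to suicide risk or to mental health. For example, it states that "sexual minority youth are more than twice as likely to attempt suicide than their heterosexual counterparts". It also presents service connection as a predictor of better functioning. What is at stake is precision that the urn has already paid for, not the validity of a positive result.

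**Working it through.** **Inputs from the article.** N = 300, 150 per arm; five time points; attrition of 10, 15, 15 and 20% at 3, 6, 9 and 12 months; slope coefficient 0.20; power 0.98.

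**Assumptions, because the article gives no figure.** Two-sided alpha of 0.05. Intercept, slope and residual variances. R², the share of variance between youths in slope that the four factors jointly explain, shown from 0 to 0.20. Factor prevalences of 0.5, 0.5, 0.5 and 0.35. An urn that starts with one ball per arm and adds one after each assignment.

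**1. The plan's own figure.** The 0.98 cannot be rebuilt without the variances. With intercept variance 0.5, slope variance 0.1 and residual variance 0.5, and dropout at the stated rates, a linear growth model gives a slope standard error of 0.0485. Power is Φ(0.20/0.0485 − 1.96) = Φ(2.16) = 0.985. So 0.98 is attainable. Other assumed variances (slope variance 0.2, or residual variance 1.0) give 0.89 to 0.95.

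**2. Ceiling, if balance were exact.** Unadjusted standard error / true standard error = 1/√(1 − R²). True type I error = 2[1 − Φ(1.96/√(1 − R²))].

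**3. Urn, which balances only in part.** 4,000 simulated trials per setting, with one slope per youth compared between arms by least squares.

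**4. Power after adjustment, if 0.98 is the unadjusted value.** The standardised effect is 2.054 + 1.96 = 4.014. Adjusted power = Φ(4.014/√(1 − R²) − 1.96). At R² = 0.20 this is Φ(4.014 × 1.118 − 1.96) = Φ(2.53) = 0.994.

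| R² (assumed) | SE ratio, exact balance | Type I, exact balance | SE ratio, urn | Type I, urn | Power after adjustment |
|---|---|---|---|---|---|
| 0 | 1.000 | 0.050 | no inflation | no change | 0.980 |
| 0.05 | 1.026 | 0.044 | about 1.02 | about 0.044 | 0.985 |
| 0.10 | 1.054 | 0.039 | about 1.03 | about 0.044 | 0.988 |
| 0.20 | 1.118 | 0.028 | about 1.07 | about 0.038 | 0.994 |

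**Checks on the simulation.** At R² = 0.20, simple randomisation gave a ratio of 0.99 and type I error of 0.051, so balancing is what makes the unadjusted test conservative. Stratified blocks gave 1.123 and 0.027, in line with the ceiling. Monte Carlo error is about 1% on the ratios and √(0.05 × 0.95/4000) = 0.003 on the error rates, so the R² = 0.05 row is barely distinguishable from no effect.

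**What R² refers to.** In the simulation it is the share of variance in the per-youth slopes analysed, which includes measurement error. At R² = 0.20 the adjusted and unadjusted model standard errors were 0.0401 and 0.0447, and 1 − (0.0401/0.0447)² = 0.195. If R² is instead taken as a share of true slope variance, the effect is smaller. With slope variance 0.1, and residual variance 0.5 over times coded 0 to 4, the error adds 0.5/10 = 0.05. The exact-balance ratios become √(0.15/0.145) = 1.017, √(0.15/0.14) = 1.035 and √(0.15/0.13) = 1.074.

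**The case against.** The strongest reply is that this is a condensed article, that a covariate list usually sits in the analysis plan, and that no sentence says the primary model is unadjusted. A reader might infer that the plan fixes a model with condition alone. The article does not say that, and outreach worker may be added. The omission of the urn factors is an inference, though a strong one. The power model has condition as its covariate, the Aim 1 text names no other, and adding each factor with its direct effect in Aim 3 would be partly redundant if all four were already present. The article also names covariates where it wants them: baseline mediators and outcomes in Aim 2, and outreach worker by rule.

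A reader might also infer that the standard errors must be too large. The documents do not support that. The hypothesis concerns change over time, and power is given for the slope. The Introduction relates sex, race and sexual orientation to levels of risk, not to rate of change over 12 months. Service connection comes nearest to a predictor of trajectory, but no figure is given. Factors that predict only level leave the slope standard error essentially unchanged.

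Two larger sizes are tempting. An excess of 2.6% to 11.8% needs near-exact balance, which an urn does not deliver and which dropout can loosen further. A power gain counted from 80% starts from a figure that the article does not state.

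**Conclusion.** The point holds as a low-severity improvement. The urn factors are not among the predictors named for Aim 1, and leaving them out makes the slope test conservative to the extent that they predict slope. The excess in the standard error is about 2% to 7% for an assumed R² of 0.05 to 0.20 under the simulated urn, with true type I error of about 0.044 to 0.038. It is nil at R² = 0. On the stated power of 0.98 the gain from adjustment is at most about 1.5 points (0.994 − 0.980 = 0.014). It could be larger if the true variances put power below 0.98.

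The treatment estimate is not biased by the omission and the false-positive rate is not raised, so nothing here undermines a significant result. The sizes rest on the assumed R², alpha, variances, factor prevalences and urn settings, none of which the article gives.

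**What to change.** In {20a}, Study aim 1, state that the intercept and slope growth factors are regressed on condition plus baseline service connection, sex at birth, race and sexual-minority status, coded as in the urn program, for the primary and secondary outcomes. Keep Aim 3 as the place for the interactions.

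The data are already collected at baseline. The cost is at least four extra parameters per growth factor, so at least 4 × 2 = 8 over intercept and slope, which N = 300 can carry. It is more if race has more than two levels in the urn. The article records race/ethnicity but does not give the urn coding, so that coding should be stated too. Naming the covariates now also removes a later choice between adjusted and unadjusted results.

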### Interim analyses {21b}

No interim analyses are planned.

### Methods for additional analyses (e.g., subgroup analyses} {20b}

#### Outreach worker effects

To ensure that differences between outreach workers are not affecting improvements in main variables of interest and engagement into treatment, analyses between them will be conducted prior to the planned statistical tests. Using outreach worker as the independent variable and number of completed sessions and suicidal ideation at the 6-month follow-up (end of treatment) as the dependent variables, an analysis of variance will be conducted to examine differences. If there is a significant effect, then outreach worker will be used as a control variable in the planned latent growth models and mediation models. Otherwise, outreach workers will not be controlled in the analyses.

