### Trial design {8}

The study is designed as a randomized controlled, parallel group, two-arm, superiority trial. All youth (*N* = 300) will be randomly assigned to the cognitive therapy for suicide prevention (CTSP) + SAU (*n* = 150) or to SAU alone (*n* = 150). SAU includes outreach, advocacy, and service linkage and is the standard intervention among providers serving populations experiencing homelessness [35]. The design of this study will allow us to test the intervention as an add-on to standard community-based services (SAU) so that the unique needs of these underserved youth are addressed in a holistic fashion. Advocates will be embedded in condition in order to reduce potential contamination. That is, only advocates trained in CTSP will deliver CTSP + SAU. And finally, as the SAU mirrors that used by shelters and drop-in centers, if the intervention shows significant effects above and beyond SAU, evidence for disseminating the intervention to drop-in centers around the country will be provided. As the intervention is manualized and uses cognitive behavioral strategies, portability is enhanced. SAU and CTSP intervention meetings must be completed by 6 months post-baseline. Self-report questionnaires and interviews will be conducted at baseline and at 3, 6, 9, and 12 months post-baseline. An intent to treat design will be followed so that all youth, regardless of participation in the intervention conditions, will be tracked for follow-up. Please see Fig. 2 below.

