### Intervention description {11a}

#### Services as usual (SAU)

Services as usual (SAU) includes standard suicidal ideation practice. Outreach, engagement, and service linkage is standard intervention for finding and engaging those experiencing homelessness into services [35]. The goal of the outreach worker is to engage homeless youth through non-office contact in sandwich lines/soup kitchens, homeless camps, libraries, and parks and encourage youth to accept the next level of service. We refer to outreach workers as advocates, because they do more than outreach. Once an individual is engaged in the current project, the outreach worker/advocate will continue to work with the client for 6 months, helping youth to secure needed services and remaining a support for the youth as he/she traverses the system of care. The approach used here, Strengths-based Outreach and Advocacy (SBOA), follows the Strengths Model [39] which focuses on client strengths rather than deficits and ensures that the youth directs the services they receive.

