#### Cognitive Therapy for Suicide Prevention (CTSP) + SAU

In the experimental condition, youth will receive SAU in addition to CTSP [23]. CTSP asserts that maladaptive cognitions lead to maladaptive emotional and behavioral responses. Furthermore, suicidal behaviors rather than underlying conditions are the primary focus. Therefore, CTSP seeks to identify triggers for suicidal behaviors, primarily targeting those cognitions associated with core beliefs and automatic negative thoughts. Therapists help youth replace negative cognitions with alternative, more adaptive ones which are expected to lead to positive behavioral change. CTSP is offered in ten sessions, but, similar to Stanley et al. [37] and Brent et al. [40], youth will be offered up to nine additional maintenance sessions within the first 6 months post-baseline. A crisis plan is developed in the first session and is expanded as therapy progresses. It includes emergency contact numbers as well as positive coping behaviors, such as walking or listening to music that the client can perform alone. Consistent with the Interpersonal Theory of Suicide [41] and Rudd’s theory [19], the experience of prior suicidal behaviors is considered associated with increased risk for future suicide attempts. Therefore, assessment of recent suicidal thoughts and behaviors is conducted every session. Clients in need of additional mental health treatment or services are referred to those respective agencies.

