#### Training and supervision

Training in CTSP will only be offered to those who will deliver CTSP in order to prevent contamination. Training consists of readings (manual/book) [23], a 3-day training in the intervention, including role play exercises and ongoing bi-weekly supervision. Master’s-level providers will be hired from the field with experience working with homeless populations and a comfort with nontraditional settings. Providers of CTSP + SAU and SAU will also participate in a 2-day training by the PI ([name]) on engagement, tracking, and service linkage. Training will include in vivo observation and modeling by PI [name] to ensure they are comfortable identifying and engaging youth. Readiness for conducting the interventions independently will be determined by the advocate in consultation with the PI.

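### The outreach-worker ANOVA pools across arms although each worker serves one arm, and its stated consequence, worker as a control variable, is collinear with treatment unless worker is nested in condition

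*Protocol article*

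**What the plan says.** Three parts of the protocol article bear on this.

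- **Who delivers what.** Trial design {8}: "Advocates will be embedded in condition in order to reduce potential contamination". Training and supervision: "Training in CTSP will only be offered to those who will deliver CTSP in order to prevent contamination". The SAU description makes outreach workers and advocates the same people: "We refer to outreach workers as advocates, because they do more than outreach". Each worker therefore sits in one arm.
- **The preliminary test.** Outreach worker effects (under {20b}) plans an ANOVA, before the main tests, with outreach worker as the factor and "number of completed sessions and suicidal ideation at the 6-month follow-up (end of treatment) as the dependent variables". Both variables are measured after randomisation. The text does not restrict the comparison to workers in the same arm.
- **The consequence.** "If there is a significant effect, then outreach worker will be used as a control variable in the planned latent growth models"; the same sentence extends this to the mediation models. If the test is not significant: "Otherwise, outreach workers will not be controlled in the analyses".

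Study aim 1 takes the treatment effect on intercept and slope from those same growth models. Study aim 2 takes the path from treatment to cognitive distortions (path a) from the mediation models.

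**The concern.** The rule has two parts, and both clash with the nesting of workers in arms.

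1. **The trigger.** When workers are nested in arm, the between-worker sum of squares splits into an arm component and a within-arm worker component. A pooled ANOVA cannot tell them apart. It can be significant because CTSP works, even when all workers in the same arm perform identically.
2. **The response.** The indicators of the CTSP workers add up to the arm indicator. With arm and ordinary worker indicators in the same model, there is no unique arm coefficient.

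At stake is the primary comparison. The larger the CTSP effect, the likelier the plan is to enter the branch in which that effect may not be identified. Leaving the rule at that point would be an unplanned choice in a trial that states it has no blinding.

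**Working it through.** The protocol gives no figure for this rule to reproduce. Its power of 0.98 for the slope effect is not in question here, and nothing below depends on it.

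**Inputs from the document**
- N = 300, 150 per arm; 15% attrition at 6 months, so 300 × 0.85 = 255 youths in the ideation ANOVA (Sample size {14}).
- Cited effects on suicidal ideation: d = 0.64 to 1.03 (same section).
- Each worker in one arm (Trial design {8}; Training and supervision).

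**Assumptions, not in the document**
- k = 1 to 5 workers per arm, equal caseloads, two-sided alpha 0.05, and no true differences between workers in the same arm.

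**Step 1: how often the arm effect alone triggers the rule.** The pooled one-way ANOVA over 2k workers has df1 = 2k − 1 and df2 = 255 − 2k. With only an arm difference d, the noncentrality is λ = 255 × d²/4. At d = 0.64, λ = 255 × 0.4096/4 = 26.1. With k = 3 the 5% critical value of F(5, 249) is 2.25, and the probability of exceeding it is 0.987.

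| d | λ | k = 1 | k = 3 | k = 5 |
|---|---|---|---|---|
| 0.3 | 5.7 | 0.67 | 0.41 | 0.31 |
| 0.5 | 15.9 | 0.98 | 0.88 | 0.79 |
| 0.64 | 26.1 | 0.999 | 0.987 | 0.964 |
| 1.03 | 67.6 | 1.00 | 1.00 | 1.00 |

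Without any arm or worker effect, this would be 0.05.

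**Step 2: completed sessions.** This may be a second trigger, because ten CTSP sessions and up to nine more are offered in one arm only. Its size cannot be computed: the document gives neither an expected number of SAU meetings nor an SD, and it does not define a completed session for this test.

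**Step 3: arm plus worker indicators.** With 3 workers per arm, the columns are the intercept, arm and 5 worker indicators: 7 columns, rank 6. With k = 1, 2, 4 and 5 the columns/rank are 3/2, 5/4, 9/8 and 11/10, always one short. In the growth model, with each column also multiplied by time, the deficit is two, one each for intercept and slope (14 columns, rank 12 at k = 3).

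**Step 4: if software drops indicators to obtain a fit.** The arm coefficient becomes the difference between the two reference workers. In one simulated data set with 3 workers per arm and an observed arm mean difference of −0.45, five choices of the omitted pair gave coefficients from −0.26 to −0.73.

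**Step 5: nested coding.** With the same 300 youths and 3 workers per arm, worker contrasts that sum to zero within arm give 6 columns, rank 6. The standard error of the arm effect, in units of the residual SD, is 0.1155, the same as with no worker terms: √(1/150 + 1/150) = 0.1155. The defect therefore lies in how worker is entered, not in adjusting for worker as such.

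**The case against.** The strongest reply is that a control variable is not defined. The article names neither indicators, nested contrasts, a random effect nor a cluster adjustment, and coding of that kind is often left to the analysis plan. A singular model would also normally show itself when fitted. A reader might infer that the treatment effect can no longer be estimated once the rule fires. The documents do not support that: Step 5 shows that fixed worker effects nested in arm keep the arm effect estimable with an unchanged standard error under equal caseloads. Nor is a fixed worker term always wrong.

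Three further inferences also go too far.
- **That the trigger is certain.** It is near-certain only at the effect sizes cited from earlier work; at d = 0.3 the probability is 0.31 to 0.67.
- **That session counts are bound to differ between arms.** Sessions offered are not sessions completed, and SAU meetings are not quantified. If only CTSP sessions are counted, among CTSP workers, that comparison is already within arm.
- **That power falls by a computable amount.** This would require the analyst to report a contrast between two reference workers as the CTSP effect, with a number of workers the document does not give.

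What stands is that the article does more than leave detail open. It fixes a test that pools across arms and a response that, in the usual sense of controlling for a categorical factor, is collinear with treatment. Nothing in the text nests worker in condition.

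**Conclusion.** The rule is wrong as written and should be changed. The pooled ANOVA cannot separate a worker effect from the treatment effect: at the protocol's own cited effects, the arm difference alone makes it significant with probability 0.96 to 1.00. If worker then enters as ordinary indicators, the arm coefficient in the growth models and path a in the mediation models are not identified, or turn into a contrast between reference workers. The rank deficit holds for any number of workers. The trigger probabilities rest on the assumed 1 to 5 workers per arm, equal caseloads, alpha 0.05 and no worker differences within arm. The conclusion is conditional on the coding: worker nested in condition would keep the arm effect estimable, but the text does not say this.

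**What to change.** - Delete the rule that a significant pooled ANOVA puts outreach worker into the models as a control variable.
- Compare workers only within condition.
- State that any worker adjustment in the growth and mediation models is nested in condition: a random effect or cluster term, or fixed contrasts summing to zero within arm. Ordinary worker indicators should not be entered alongside condition.

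This costs a few sentences and needs no new data, staff or participants. It has a statistical downside. With few workers per arm, a random-effect variance is poorly estimated, and a random or cluster term may widen the standard error of the arm effect. As an illustration, the design effect is 1 + (m − 1) × ICC with m = 255/(2k) youths per worker. An assumed ICC of 0.01 with 5 workers per arm (m = 25.5) gives 1.25, and an ICC of 0.05 with 2 per arm (m = 63.75) gives 4.14. Fixed nested contrasts avoid that widening under equal caseloads, but the result then applies to the workers in this trial. With a single worker per arm, no coding can separate worker from treatment.
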